## Abstract

**Background:**

Fimasartan is the ninth angiotensin receptor blocker to be developed. However, it has not yet been evaluated for reno-protective effects in hypertensive diabetic chronic kidney disease (CKD). The target blood pressure (BP) for hypertensive diabetic CKD is also a controversial topic. This trial was designed to assess the reno-protective effects of fimasartan compared to those of losartan as a primary outcome. This study also compares the two drugs with regard to cardiovascular and renal outcomes in accordance with target systolic BP (SBP) (as secondary outcomes).

**Methods:**

This study is a prospective, phase III, randomized, double-blind, active-controlled, non-inferiority, four-parallel group, dose-titration, multicenter trial. We recruit patients with hypertensive diabetic CKD with overt proteinuria. Participants will be randomized into four groups (1:1:1:1): fimasartan standard SBP control (SBP < 140 mmHg); fimasartan strict SBP control (SBP < 130 mmHg); losartan standard SBP control; and losartan strict SBP control. After 24 weeks, all individuals are treated with fimasartan for an additional 120 weeks in an open-label design, maintaining their assigned SBP control groups as randomized. The primary endpoint is the rate of change in proteinuria, which is assessed using the spot urine albumin–creatinine ratio at 24 weeks. The secondary endpoints are the cardiovascular and renal outcomes at 144 weeks compared between the strict SBP and standard SBP control groups.

**Discussion:**

The FANTASTIC is a clinical study to provide: (1) the reno-protective effect of fimasartan; and (2) the target BP to reduce adverse outcomes in hypertensive diabetic CKD with overt proteinuria.

**Trial registration:**

Clinicaltrials.gov, NCT02620306. Registered on 1 December 2015.

**Electronic supplementary material:**

The online version of this article (doi:10.1186/s13063-017-2375-8) contains supplementary material, which is available to authorized users.

## Background

Hypertension affects approximately 40% of adults worldwide [1] and about two-thirds of patients with diabetes have concomitant hypertension [2]. Both hypertension and diabetes have a variety of vascular complications, including macrovascular and microvascular effects. The macrovascular complications of hypertension and diabetes include coronary artery disease, stroke, and peripheral vascular disease. The microvascular complications include retinopathy, nephropathy, and neuropathy. Hypertension and diabetes also increase the risk of developing new-onset chronic kidney disease (CKD) [3]. The progression of CKD is accompanied by microvascular complications. CKD increases a patient’s risk of stroke, coronary artery disease, and all-cause mortality. The annual mortality rate of those patients who progress to require dialysis is about 10–20% [4, 5].

Given the association between CKD and cardiovascular disease, it is important to suppress CKD progression in patients with both hypertension and diabetes. The degree of baseline proteinuria is correlated to the future progression of CKD [6–8]. High albuminuria was shown to be associated with increased risk of myocardial infarction, stroke, first hospitalization for heart failure, unstable angina, coronary or peripheral revascularization, and cardiovascular death [9]. Recent evidence has shown that reducing proteinuria can prevent the progression of CKD. Angiotensin II receptor blockers (ARB) have also been shown to reduce CKD progression of CKD [10–14]. Most hypertension guidelines recommend that angiotensin converting enzyme inhibitors (ACEI) or ARBs be used in patients with hypertensive diabetes [15–17]. There are few studies that directly compare the renal efficacy of two ARBs in hypertensive diabetes. In one comparison study of hypertensive type 2 diabetic patients with overt nephropathy, telmisartan were found to have similar renal efficacy to valsartan [18]. In another comparison study, telmisartan was found to be superior to losartan at reducing the geometric mean urinary protein–creatinine ratio without a change in blood pressure (BP), dietary sodium, or estimated glomerular filtration rate (eGFR) [19]. Therefore, although ARBs have a reno-protective class effect, there are relative differences in each drug’s efficacy.

Fimasartan was the ninth ARB approved for the treatment of hypertension by the Korean Ministry of Food and Drug Safety in 2010; it entered the market in 2011 [20]. Its chemical characteristics are as follows: 2-n-butyl-5-dimethylaminothiocarbonyl methyl-6-methyl-3-([2’-(1H-tetrazol-5-yl) biphenyl-4-yl] methyl) pyrimidin-4(3H)-one); molecular formula, C27H31N7OS; molecular weight, 501.65; formally known as BR-A-657. Despite the proven antihypertensive effect, however, the renal efficacy and safety of fimasartan in hypertensive diabetic CKD have not been studied or compared to those of other ARBs. Therefore, this randomized multicenter clinical trial compares the renal efficacy and safety of fimasartan to those of losartan, which has already been shown to have a renal protective effect [12].

The target BP in diabetic CKD remains controversial. There are inconsistencies in the current guidelines regarding target BP for patients with diabetic CKD from KDIGO (Kidney Disease Improving Global Outcomes), ESC (European Society of Cardiology), and JNC (Joint National Committee) 8 [15, 16, 21]. The current KDIGO guideline recommends that the target goal is a systolic BP (SBP) < 130 mmHg and diastolic BP (DBP) < 80 mmHg in diabetic CKD, with a urine albumin excretion > 30 mg/day. [21] The JNC 8 panel recommends that hypertensive adults with diabetic or non-diabetic CKD keep their BP < 140/90 mmHg. [15]

Thus, the purpose of the present study, FimAsartaN proTeinuriA SusTaIned reduCtion in comparison with losartan in diabetic chronic kidney disease (FANTASTIC) trial, is to investigate the reno-protective effect of fimasartan in comparison with losartan in patients within a diabetic CKD group and we also aim to evaluate the long-term effect of strict SBP control on renal and cardiovascular outcomes in comparison with standard SBP control.

## Methods

### Study design

The FANTASTIC study is a randomized, multi-centered, double-blind, four-parallel group, dose-titration, phase III study. This study was designed to compare the efficacy of fimasartan (study group) and losartan (control group) with regard to the rate of change in proteinuria. It also compares the adverse outcomes between strict BP control and standard BP control in patients with hypertensive diabetic CKD with overt proteinuria. Forty clinical research centers (19 nephrology, 14 cardiology, and seven endocrinology) participated in this trial and all research centers are comprised of the tertiary university hospital. This study is sponsored by an investigator-initiated grant by Boryung Pharmaceutical Co., Ltd. It was registered at http://www.clinicaltrials.gov/ before participant recruitment (NCT02620306). All participants will provide written informed consent based on documents approved by each university Institutional Review Board.

### Study eligibility

#### Inclusion and exclusion criteria

Patients are screened for the following four required conditions: high BP; CKD; overt proteinuria (or macroalbuminuria); and type 2 diabetes mellitus. The detailed inclusion criteria are described in Table 1. The exclusion criteria are described in Table 2. Finally, after learning about the study, patients voluntarily provided written consent to participate.

**Table 1 Tab1:** Inclusion criteria

Age: 19–70 years
Screening visit (Visit 1)
Hypertension in treatment-naïve patients
140 mmHg ≤ SBP < 180 mmHg and DBP < 110 mmHg
Hypertension with treatment, including ACEI/ARB
130 mmHg ≤ SBP < 180 mmHg and DBP < 110 mmHg
eGFR ≥ 30 mL/min/1.73 m^2^ (by MDRD) within the past six months
Urine protein (within the past six months)
ACR ≥ 300 mg/g (or mg/day)
or protein–creatinine ratio ≥ 500 mg/g (or mg/day)
Type 2 diabetes mellitus (diagnosed > 3 months prior) on medications with
no changes in medication regimen/dose within the last three months
Baseline visit (Visit 3)
Hypertension
140 mmHg ≤ SBP < 180 mmHg and DBP < 110 mmHg
eGFR ≥ 30 mL/min/1.73 m^2^ (by MDRD)
Urine protein: ACR ≥ 300 mg/g in spot urine
Type 2 diabetes without regimen change during placebo run-in period

*SBP* systolic blood pressure, *DBP* diastolic blood pressure, *ACEI* angiotensin converting enzyme inhibitor, *ARB* angiotensin receptor blocker, *ACR* albumin–creatinine ratio, *eGFR* estimated glomerular filtration rate, *MDRD* Modification of Diet in Renal Disease

**Table 2 Tab2:** Exclusion criteria

Secondary or malignant hypertension
Inter-arm BP difference: SBP > 20 mmHg or DBP > 10 mmHg
Symptomatic orthostatic hypotension
Cardiovascular history
MI, congestive heart failure (NYHA class III or IV), CABG, PTCA, or angina < 3 months before enrollment
Severe cerebrovascular disease (stroke, cerebral infarction, or cerebral hemorrhage)
Arrhythmia (significant ventricular tachycardia, atrial fibrillation, or atrial flutter)
Significant valvular disease: aortic stenosis or mitral stenosis
Hypertrophic cardiomyopathy
Type 1 DM or HbA1c > 9% at screening
Significant renal or hepatic disease
Dialysis, cirrhosis, biliary tract obstruction, cholestasis, or liver failure
eGFR (MDRD) < 30 mL/min/1.73 m2, hyperkalemia (>5.5 mmol/L) or hypokalemia (<3.5 mmol/L)
AST or ALT > 3 times the upper limit of normal
Any chronic inflammatory disease requiring chronic anti-inflammatory treatment (including rheumatoid arthritis, systemic lupus erythematosus, or connective tissue disease)
Moderate or malignant retinopathy < 6 months before enrollment (e.g. moderate or severe non-proliferative diabetic retinopathy and proliferative diabetic retinopathy)
Surgical or medical disease that may affect drug absorption, distribution, metabolism, or excretion
Cancer history with current treatment or treatment within five years
Pregnancy, childbearing potential without adequate contraception, or breast-feeding
Previous hypersensitivity reaction to renin-angiotensin system inhibitors
Alcohol or drug abuse within the previous two years
Poor compliance during placebo run-in period: < 70%

*SBP* systolic blood pressure, *DBP* diastolic blood pressure, *MI* myocardial infarction, *NYHA* New York Heart Association, *CABG* coronary artery bypass graft, *PTCA* percutaneous coronary angioplasty, *DM* diabetes mellitus, *eGFR* estimated glomerular filtration rate, *MDRD* Modification of Diet in Renal Disease, *AST* aspartate transaminase, *ALT* alanine transaminase

### Screening

Included individuals go through a single-blind placebo run-in period for at least four weeks. During this period, any treatment with ACEI/ARBs for hypertension will be discontinued. However, other antihypertensive drugs are administered without changing the regimens or doses. During the placebo run-in period, the participant is instructed to measure his/her own BP with a provided oscillometric automatic device more than once a day. Individuals are instructed to visit the study site in the event of SBP ≥ 180 mmHg or onset of any symptoms of suspected hypertension (e.g. headache, dyspnea, chest discomfort, vomiting, and neurologic symptoms). In this situation, additional antihypertensive drugs (other than ACEIs/ARBs) are introduced or adjustments were made to the doses of the patient’s other medications as appropriate. After the placebo run-in period is completed for at least four weeks, tests for eligibility assessment are performed at the visit before baseline (Visit 2).

#### Randomization

The individuals are finally selected at baseline (Visit 3). An independent group not involved with study implementation creates a randomization schedule for study drug labelling and randomization is stratified by study site. Eligible participants are randomized into one of the following four groups in a 1:1:1:1 ratio using the interactive web-based randomization system, Fimasartan group A, Fimasartan group B, Losartan group A, and Losartan group B. Group A is a standard BP control group (SBP < 140 mmHg), while Group B is a strict BP control group (SBP < 130 mmHg). The randomized participants are treated with the investigational product (fimasartan or losartan) corresponding to each treatment group for 24 weeks on double-blind (physician and patient). After that, all individuals take fimasartan for an additional 120 weeks in an open-label study conducted with two groups (in accordance with BP control). The eligible participants provide written consent for participation in the open-label study and clinical study (Fig. 1).

**Fig. 1 Fig1:**
[figure not shown]
*Flow chart* of FANTASTIC study. The FANTASTIC study consists of two phases: four-parallel double-blind period to investigate the reno-protective effect of fimasartan and two-parallel open-label period for prognosis in accordance with target BP. **a** Standard BP control group (systolic BP < 140 mmHg). **b** Strict BP control group (systolic BP < 130 mmHg). FIM fimasartan, LOS losartan, CCB calcium channel blocker, ACR albumin–creatinine ratio, CV cardiovascular, SBP systolic blood pressure

**Fig. 2 Fig2:**
[figure not shown]
Standard Protocol Items: Recommendations for Interventional Trials (SPIRIT) figure. BP blood pressure, BUN blood urea nitrogen, ECG electrocardiography, eGFR estimated glomerular filtration rate

### Methods of dose administration

Either the study drug (fimasartan 60 mg/day) or control drug (losartan 50 mg/day) is administered at the time of randomization and maintained during the double-blind study period. The dose is titrated if the patient BP dose not meets the targeted level at each visit after Visit 4. The dose titrations are made at the discretion of the investigator based on the measured SBP. Fimasartan 60 mg or losartan 50 mg are uptitrated to fimasartan 120 mg or losartan 100 mg, respectively. At subsequent visits, additional antihypertensive therapy is added, excluding ACEIs or ARBs, in the following order: dihydropyridine calcium channel blockers; diuretics; β-blockers; α-blockers; and direct vasodilators (see Fig. 1). When additional antihypertensive drugs are administered, the dose is increased one level at a time. If the additional medication is still needed before the next visit because of continued uncontrolled BP, the dose can be titrated to the next level by making an unscheduled visit. This decision is made by the investigator. The investigator can also change the order of additional drugs administered in consideration of any antihypertensive drug that the subject have already taken. The drug dose can also be decreased in order to satisfy the BP control criteria or in the case of adverse events. However, the doses of other antihypertensive drugs (excluding fimasartan/losartan) are the first to be decreased when doses are adjusted. The doses of fimasartan and losartan are not changed if possible. Any individuals who cannot tolerate the BP control process does not continue the clinical study.

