### Primary and secondary endpoints

The primary endpoint is the rate of change in proteinuria in the fimasartan group and the losartan group from baseline to 24 weeks.

The major secondary endpoints are cardiovascular composite endpoints and renal composite endpoints. The cardiovascular composite endpoints are defined as the time to the first occurrence of any of the following (in accordance with the BP control criteria): myocardial infarction; stroke; hospitalization due to heart failure; unstable angina; coronary revascularization; peripheral revascularization; or all-cause mortality. The renal composite endpoints include any of the following (in accordance with the BP control criteria): the time to serum creatinine concentration doubling from baseline; the time to progression to end stage renal disease (ESRD) (as confirmed by the initiation of long-term dialysis or renal transplantation); and all-cause mortality.

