### Statistics

In order to achieve a statistical power of 80%, the sample size assumed a non-inferiority margin of 18% (based on two-sided t test and a significance level of 0.025). This is based on the rate of change in proteinuria from baseline (Week 0) to week 24 of both losartan and fimasartan groups with a standard deviation of 62% [10, 12–14, 23]. Based on the assumption of a drop-out rate of 20%, a total of 468 patients are needed for randomization (with 234 patients per treatment arm).

The primary efficacy assessment finds that the fimasartan group is not inferior to the losartan group if the lower limit of a 95% two-sided confidence interval for the difference in the rate of change in proteinuria at week 24 between the fimasartan and losartan groups (control group - study group) is > − 18%. This is defined as the non-inferiority margin.

The major secondary efficacy assessment is determined by the incidence of combined cardiovascular and renal composite endpoints and is assessed using Kaplan–Meier curves, according with target BP at 144 weeks. The median survival time and confidence interval for the median survival time are presented. The log-rank test is used to compare the groups. Other secondary efficacy assessments are determined using the following methods. For continuous variables, descriptive statistics (number of individuals, mean, standard deviation, median, minimum, and maximum) for each time point are provided according to treatment group or the BP control criteria. The t-test is used to compare the inter-group difference in the rate of change. The inter-group difference in the amount of change is tested using the analysis of covariance, with the baseline values as covariates and the treatment groups as factors. The least squared mean and standard error are provided for each group. Frequencies and ratios are provided for categorical variables such as the proportion of individuals. For categorical variables, the Chi-square test, Fisher’s exact test, or Cochran–Mantel–Haenszel test is performed.

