The target BP level in diabetic CKD is controversial. Previous studies, including the MDRD and African American Study of Kidney Disease and Hypertension (AASK), compared standard BP control with intensive BP control in CKD. The MDRD study included patients with non-diabetic CKD stage 3 or 4 and employed either standard target BP control (of ≤ 140/90 mmHg with mean arterial pressure (MAP) ≤ 107 mmHg) or intensive BP control (of 125/75 mmHg with MAP ≤ 92 mmHg). There was no difference in the progression of CKD between the standard and intensive BP control groups [27]. However, in post hoc analysis of the MDRD study, intensive BP control was beneficial in the progression of CKD in accordance with the degree of proteinuria. Patients with proteinuria of 0.25–1.0 g/d were advised to aim for a target BP of approximately < 130/80 mmHg [8].

AASK consisted of CKD stage 3 (GFR of 20–65 mL/min/1.73 m^2^) in African Americans with hypertension. The standard target BP was ≤ 140/90 mmHg (MAP ≤ 107 mmHg), and intensive target BP was 125/75 mmHg (MAP ≤ 92 mmHg). There was no difference in the progression of CKD between the standard and intensive BP control groups [28]. However, the long-term AASK data demonstrated that the intensive BP control group with proteinuria (urine protein–creatinine ratio > 0.22) had a lower incidence of ESRD than did the normal BP control group [29]. These finding suggest that it is necessary to adjust the target BP in CKD patients depending on the degree of proteinuria.

The KDIGO guideline recommends that the target BP goal in patients with diabetic CKD with urine albumin excretion > 30 mg/day is a SBP < 130 mmHg and DBP < 80 mmHg [21]. The ESC guidelines recommend target goals of SBP < 140 mmHg in CKD or non-CKD, SBP < 130 mmHg when overt proteinuria is present, and DBP < 85 mmHg in diabetes [16]. However, in the Action to Control Cardiovascular Risk in Diabetes (ACCORD) trial, patients treated with intensive BP control (SBP < 120 mmHg) and those with eGFR < 30 mL/min/1.73 m^2^ experienced more hypotension than did those with standard BP control. Intensive BP control also did not reduce the cardiovascular outcomes [30]. This result is reflected in JNC 8. Panels of JNC 8 recommend the same threshold for hypertensive adults with diabetic or non-diabetic CKD at < 140/90 mmHg [15].

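### Patients who cannot tolerate BP control leave the whole study, which puts the 144-week strict-versus-standard event comparison at risk of informative, arm-dependent censoring

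*Protocol article*

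**What the plan says.** All references are to the Protocol article.

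- **Exit rule** (Methods of dose administration): "Any individuals who cannot tolerate the BP control process does not continue the clinical study". It is not limited to study drug, titration or the BP target, and it covers both BP arms. The same paragraph allows a softer step: "The drug dose can also be decreased in order to satisfy the BP control criteria or in the case of adverse events".
- **Randomised BP target** (Randomization): "Eligible participants are randomized into one of the following four groups in a 1:1:1:1 ratio". Two of the four groups aim for SBP below 140 mmHg and two for SBP below 130 mmHg, so strict versus standard is 1:1. The Abstract says the BP groups are kept through the open-label phase to week 144.
- **Who knows the target** (Follow-up): BP control is only single-blinded, because the investigator has to check each patient's target at every visit.
- **Endpoints** (Primary and secondary endpoints): "The cardiovascular composite endpoints are defined as the time to the first occurrence of any of the following", and the list includes all-cause mortality. The renal composite covers doubling of serum creatinine, ESRD and all-cause mortality.
- **Analysis** (Statistics): Kaplan–Meier curves by target BP at 144 weeks. "The log-rank test is used to compare the groups".
- **Follow-up after exit**: the article describes none.

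**The concern.** Kaplan–Meier and the log-rank test treat a patient who leaves as having the same future risk as those who stay in the same arm. Here the reason for leaving is a consequence of the randomised factor. Baseline SBP must be at least 140 mmHg (Table 1). A patient who comes down to 130–139 mmHg has met the standard target but is still titrated in the strict arm, so the strict arm can be expected to receive more treatment. More intolerance there is plausible, and patients made unwell by BP lowering may well differ in prognosis from those who are not. The judgement is made by someone who knows the arm.

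The target BP that reduces adverse outcomes is one of the trial's two stated aims (Abstract, Discussion; end of Background). If later deaths, dialysis starts and creatinine values of the leavers are never collected, no analysis can recover them. Weighting or sensitivity analyses could only explore what might have happened.

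**Working it through.** **1. The plan's own figure.** The only sizing is for the primary drug comparison: margin 18%, SD 62%, power 80%, drop-out 20% (Statistics). With one-sided alpha 0.025:

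n per arm = 2 × (1.960 + 0.842)² × 62² / 18² = 2 × 7.849 × 3844 / 324 = 186.2, rounded up to 187.

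187 / 0.80 = 233.75, rounded up to 234; 2 × 234 = 468. This matches the stated 468. With 1:1:1:1 allocation there are also 234 patients per BP arm. The drop-out figure is not split by BP arm, and no event rate is given.

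**2. Illustrative model.** Every input below except the 234 and the 144 weeks is an assumption.

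- True hazard ratio 1.00; 144-week event risk R = 10% or 20%.
- A fraction f = 0.25 of patients has k times the hazard h of the rest.
- Removals are percentages of randomised patients, all at week 12 and all from that stratum, applied to those still event-free.
- h solves (1 − f)·exp(−144h) + f·exp(−144kh) = 1 − R.
- The observed hazard ratio is the Mantel–Haenszel rate ratio over time.

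**3. One case by hand.** R = 20%, k = 3, removal 15% strict versus 5% standard.

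- 144h = 0.1544, since 0.75 × 0.8569 + 0.25 × 0.6293 = 0.800. So h = 0.001072 per week.
- Just after week 12, lower-risk patients at risk in each arm: 0.75 × 0.9872 = 0.7404.
- Higher-risk patients at risk: strict (0.25 − 0.15) × 0.9621 = 0.0962; standard (0.25 − 0.05) × 0.9621 = 0.1924.
- Mean hazard in units of h: strict (0.7404 + 3 × 0.0962) / 0.8366 = 1.230; standard (0.7404 + 3 × 0.1924) / 0.9328 = 1.413.
- Ratio at that moment: 1.230 / 1.413 = 0.871. Taken over all 144 weeks, including the first 12 at 1.00, the observed hazard ratio is 0.892.

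**4. Range (true hazard ratio 1.00 throughout).**

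| Removed, strict vs standard | R = 10%; k = 2, 3, 4 | R = 20%; k = 2, 3, 4 |
|---|---|---|
| 5% vs 2% | 0.983, 0.971, 0.962 | 0.983, 0.972, 0.964 |
| 10% vs 3% | 0.957, 0.927, 0.906 | 0.958, 0.930, 0.911 |
| 15% vs 5% | 0.933, 0.887, 0.853 | 0.935, 0.892, 0.861 |
| 10% vs 10% | 1.000 | 1.000 |

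With leavers of average risk (k = 1) the result is 1.000 at every removal rate. With leavers at half the hazard (k = 0.5) it is 1.013 to 1.049 for the three unequal patterns. If everyone is followed for events, it is 1.00 in every case.

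**5. Lost events.** Full follow-up would give 234 × 0.10 = 23.4 or 234 × 0.20 = 46.8 events per arm. In the hand case the strict arm keeps 35.1 (25% lost) and the standard arm 42.9 (8% lost). Over the unequal patterns with k = 2 to 4, the strict arm loses about 7% to 30% of its events and the standard arm about 3% to 10%.

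**6. Against sampling error.** SE(log HR) = √(1/E₁ + 1/E₀), where E₁ and E₀ are the events kept in the strict and standard arms. In the hand case √(1/35.1 + 1/42.9) = 0.228, and |ln 0.892| = 0.114, which is 0.50 SE. Over the same patterns the shift runs from 0.06 to 0.65 SE.

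**The case against.** The strongest reply is that harm is not shown. A reader might infer from the rule that the strict arm will selectively lose its highest-risk patients and that the comparison is biased in favour of strict control. The documents do not support that as a fact. They give no removal rate by BP arm and no risk for those removed. The rule covers both arms, doses may be reduced first, and the investigator may change the order of added drugs. Bias needs both unequal removal and leavers whose risk differs from the rest; if either is absent there is none, and lower-risk leavers would shift the result the other way.

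The article's own evidence is indirect. The Discussion cites a trial in which patients under intensive control "experienced more hypotension than did those with standard BP control", but that target was SBP below 120 mmHg, and the sentence also concerns patients with eGFR below 30, who are excluded here. Even the larger shifts are below one standard error, and the comparison is secondary.

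A reader might also infer harm to the primary week-24 ACR comparison. That does not follow: each drug arm contains both BP targets equally, so target-driven loss is largely balanced by drug, and 20% drop-out is already in the sample size.

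Finally, a condensed article may leave follow-up after withdrawal to the full protocol. That would answer an omission. Here the article states a rule, and as published it points away from continued follow-up.

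These points limit what can be said about size and direction. They do not remove the exposure: an exit from the study tied to the randomised factor, decided with knowledge of the arm, and followed by an analysis that assumes uninformative censoring.

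**Conclusion.** The concern holds as a risk and not as a demonstrated bias. The exit sentence leaves the 144-week strict-versus-standard comparison open to informative censoring that may differ by arm, and it discards events. Under the assumed removal rates and a higher-risk leaving stratum, a true hazard ratio of 1.00 would be seen as about 0.85 to 0.98. It would be 1.00 with equal removal or average-risk leavers, and about 1.01 to 1.05 with lower-risk leavers. Those figures rest wholly on assumed event risk, removal rates, removal time and stratum hazard. What does not rest on them is that uncollected outcomes cannot be restored later, so the matter belongs in the protocol and cannot be left to the analysis.

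**What to change.** Amend the sentence in Methods of dose administration so that it separates leaving the BP strategy from leaving the study for data collection. State that, whatever the investigator decides on treatment, cardiovascular events, serum creatinine, dialysis or transplantation, and vital status are collected to week 144 for every randomised patient who still consents. State that these patients count in their randomised BP group in the Kaplan–Meier and log-rank analysis. If the full protocol already provides for this, reconcile the published sentence with it.

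This proposes no dose and no rule for stopping treatment.

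The cost is one amended sentence, plus visits, phone calls or record checks for the patients who stop; no patients are added. There was still time at the article's status date: 171 of 468 patients had been randomised by October 2017 and recruitment was continuing. It had begun in November 2015, about 100 weeks earlier, so nobody could yet have reached week 144.
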